### Overview of cognitive function measures

To evaluate the beneficial effects of combination exercise on cognitive functions, we assess a broad range of cognitive functions (Table 1). Measures of the cognitive functions are divisible into seven categories (executive functions, episodic memory, short-term memory, working memory, reading ability, attention, and processing speed). Executive functions are measured using the Stroop Test (ST) [39] and Verbal Fluency Task (VFT) [40]. Episodic memory is measured using Logical Memory (LM) [41] and First and Second Names (FS-N) [42]. Short-term memory is measured using Digit Span Forward (DS-F) [43]. Working memory is measured using Digit Span Backward (DS-B) [43]. Reading ability is measured using the Japanese Reading Test (JART) [32]. Attention is measured using the Digit Cancellation Task (D-CAT) [44]. Processing speed is measured using Digit Symbol Coding (Cd) [43] and Symbol Search (SS) [43]. Details of all tasks are described below.

**Table 1 T1:** Summary of cognitive function measures

**Cognitive function**	**Task**
Executive functions	Stroop test
	Verbal fluency task
Episodic memory	Logical memory
	First and second names
Short-term memory	Digit span forward
Working memory	Digit span backward
Reading ability	Japanese reading test
Attention	Digit cancellation task
Processing speed	Digit symbol coding
	Symbol search

We assess these cognitive function measures before and after the intervention period (four weeks). The primary outcome measure is ST, which we selected because 1) previous studies using exercise training showed that exercise training can improve executive functions [45,46], 2) ST is a task that is often used to measure executive functions [47,48], and 3) ST has been standardized, with high reliability and validity in Japanese populations [39,49].

***ST***: Stroop Test (ST) measures executive function including response inhibition and impulsivity. Hakoda's version is a paper and pencil version ST [39]. In this test, participants must check whether their chosen answers are correct, unlike the traditional oral-naming ST. We use a reverse ST and an ST. In the reverse ST, in the leftmost of six columns, a word naming a color is printed in another color (for example, ‘red’ is printed in blue letters); each of the other five columns is filled with five different colors from which participants must check the column whose color matches the written word in the leftmost column. In the ST, in the leftmost of six columns, a word naming a color is printed in another color (for example, ‘red’ is printed in blue letters) and the other five columns contain words naming colors. Participants must check the column containing the word naming the color of the word in the leftmost column. In each task, participants are instructed to complete as many of these exercises as possible in 1 min. The primary measure for this task is the number of correct items.

***VFT***: Verbal Fluency Task (VFT) measures executive function. We use the Japanese version of VFT [40], which has two tasks (the Letter Fluency Task (LFT) and Category Fluency Task (CFT)). In LFT, a Japanese letter, ‘ka’, is given to each participant, who is then asked to generate common nouns beginning with this letter - as many as possible in 60 s. In CFT, a category name (Animal) is given to each participant, who is then asked to generate many words of a certain category (Animal). The participants are instructed not to include proper nouns or to repeat one that has already been stated. The primary measure for this task is the number of words reported. The reliability and validity of Japanese LFT were demonstrated by Ito [40].

***LM***: Logical Memory (LM) evaluates the performance of episodic memory. LM is a subtest of the Wechsler Memory Scale-revised (WMS-R) [41]. LM consists of two short, paragraph-length stories (Story A and Story B). In LM, participants must memorize the short story. The stories are scored in terms of the number of story units recalled, as specified in the WMS-R scoring protocol. We use either Story A or Story B. The primary measure for this task is the number of correct story units recalled.

***FSN***: First and Second Names (FSN) evaluates memory ability in everyday life. FSN is a subset of Rivermead Behavioural Memory Test (RBMT) [42]. RBMT measures episodic memory as it is used in everyday life. Therefore, subsets of RBMT are similar to everyday situations. In FSN, participants must memorize first and second names with faces (photographs). Subsequently, they must recall the first and the second names when the face is shown again later. We use four faces (four first names and four second names). The primary measure of this test is the total number of correct answers in both first and second names. The maximum raw score of FSN is 8.

***DS*****:** Digit Span (DS) is a subtest in Wechsler Adult Intelligence Scale-third edition (WAIS-III) [43]. Digit Span, which has two subsections (DS-F and DS-B), evaluates short-term memory and working memory. DS-F measures short-term memory simply by requiring participants to repeat numbers. DS-B measures working memory by requiring participants to memorize numbers and to repeat the numbers in inverse order. For DS-F, participants repeat numbers in the same order as they were read aloud by the examiner. For DS-B, participants repeat numbers in the reverse order of that presented aloud by the examiner. In both, the examiner reads a series of number sequences which the examinee must repeat in either forward or reverse order. DS-F has 16 sequences. DS-B has 14 sequences. The primary measures of this test are raw scores that reflect the number of correctly repeated sequences until the discontinue criterion (that is, failure to reproduce two sequences of equal length) is met [43]. The maximum raw score of DS-F is 16. The maximum raw score of DS-B is 14.

***JART*****:** The Japanese Reading Test (JART) measures reading ability [32]. JART is a Japanese version of the National Adult Reading Test (NART), which has a reading test of 50 irregularly spelled words in English (for example, ache) [50]. JART is a reading test comprising 25 Kanji compound words (for example, 親父, 煙草). The reading stimuli are printed out randomly for reading. The participants are asked to read each Kanji compound word aloud. This task assesses reading ability and IQ. The primary measure for this task is the number of correct items.

***D-CAT*****:** Digit Cancellation Task **(**D-CAT) evaluates attention [44]. The test sheet consists of 12 rows of 50 digits. Each row contains five sets of numbers 0 to 9 arranged in random order. Consequently, any one digit appears five times in each row with randomly determined neighbors. D-CAT comprises three such sheets. Participants are instructed to search for the target number(s) that had been specified to them and to delete each one with a slash mark as quickly and as accurately as possible until the experimenter sends a stop signal. Three trials exist, first with a single target number (6), second with two target numbers (9 and 4), and third with three (8, 3, and 7). Each trial is given for 1 min. Consequently, the total time required for D-CAT is 3 min. In the second and third trials, it is emphasized that all the target numbers instructed should be cancelled without omission. The primary measure of this test is the number of hits (correct answers). We use only the number of hits in the first trial.

***Cd*****:** Digit Symbol Coding (Cd) is a subtest of WAIS-III [43]. This test measures processing speed. For Cd, the participants are shown a series of symbols that are paired with numbers. Using a key within a 2 min time limit, participants draw each symbol under its corresponding number. The primary measure of this test is the number of correct answers.

***SS*****:** Symbol Search (SS), a subtest of WAIS-III containing 60 items [43], measures processing speed. For this subtest, participants visually scan two groups of symbols (a target group and a search group) and report whether either of the target symbols matches any symbol in the search group. Participants respond to as many items as possible within a 2 min time limit. The primary measure of this test is the number of correct answers.

### Psychological questionnaire

To evaluate the beneficial effects of combination exercise on satisfaction and quality of life (QOL) for participants, we use some questionnaires. We ask participants to answer the questionnaires related to the subjective feelings (1; motivation of continuing the combination exercise during the intervention period, 2; fatigue during the intervention period, 3; satisfaction of the intervention during the intervention period, 4; enjoyment of the combination exercise during the intervention period) after the intervention period. Participants rate these questionnaires using a nine-point scale (for motivation scale, from 1 = very low to 9 = very high; for fatigue scale, from 1 = very low to 9 = very high; for satisfaction scale, from 1 = very low to 9 = very high; for enjoyment scale, from 1 = very low to 9 = very high). To evaluate QOL, we use Japanese versions of WHOQOL-BREF (WHO/QOL-26) [51]. The QOL-26 is a short version of the WHOQOL and is a self-rating instrument that assesses individuals’ perceptions of their position in life in the context of the culture and value system in which they live and in relation to their goals, expectations, standards, and concerns. The QOL-26 has 26 items with 5 subscales: Physical (physical state), Psychological (cognitive and affective state), Social (interpersonal relationships and social roles in life), Environmental (relationships to salient features of the environment), and Global (meaning in life, or overarching personal beliefs). A 5-point response category is used, ranging from 1, which indicates ‘strongly disagree’, to 5, which indicates ‘strongly agree’. All responses on each subscale are added within each subscale. The total score is the sum of the first 5 subscales. The QOL of the respondent is evaluated using the scores of the first 5 subscales and their total score. A higher score indicates better QOL.

### Sample size

Our sample size estimation is based on the change score in the reverse Stroop task, which is the primary outcome in this study. This study uses eta squared (η^*2*^) as an index of effect size. As a descriptive index of strength of association between an experimental factor (main effect or interaction effect) and a dependent variable, η^*2*^ is defined as the proportion of total variation attributable to the factor, and it ranges in value from 0 to 1 [52]. Using information (the sums of squares for total; SS total, the sum of squares for factor; SS factor) reported in an analysis of covariance (ANCOVA) summary table, we calculate η^*2*^ (SS factor divided by SS total). SS factor is the variation attributable to the factor and SS total is the total variation, which includes the SS factor and the sum of squares for error. In actuality, η^*2*^ ≥0.01 is regarded as a small effect, η^2^ ≥0.06 as a medium effect, and η^*2*^ ≥0.14 as a large effect [52]. We expect to detect a large effect size (η^2^ = 0.14) of the change score (post-training score minus pre-training score) in the reverse Stroop task between combination exercise and waiting list groups. The sample size was determined using G*power [53,54] based on 80% power, a two-sided hypothesis test, an alpha level of 5%, an ANCOVA model that includes a baseline reverse Stroop task score, age and sex as a covariate. The sample size calculation indicated that we need 32 participants in each of the combination exercise and waiting list groups with consideration of a 20% drop-out rate.

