### Analysis

This study is designed to evaluate the beneficial effect of the short-term combination exercise in older people. We calculate the change score (post-training score minus pre-training score) in all cognitive function measures. We conduct an ANCOVA for the change scores in each cognitive test. The change scores are the dependent variable. Groups (combination exercise, waiting list) are the independent variable. Pre-training scores in the dependent variable, sex, age categories are covariates to adjust for background characteristics and to exclude the possibility that any pre-existing difference of measure between groups affects the result of each measure. The level of significance is set as *P* <0.05. This study reports η^*2*^ as an index of effect size (please see the detail in Sample Size). Missing data are imputed using Missing Value Analysis in the Statistical Package for the Social Sciences (SPSS). In particular, we impute missing values using maximum likelihood estimation based on the expectation-maximization algorism with the observed data in an iterative process [55]. All randomized participants are included in the analyses in line with their allocation, irrespective of how many sessions they complete (intention-to-treat principle). All analyses are performed using the SPSS (version 18 or higher; SPSS Japan Inc.).

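### The reported eta squared has an ambiguous denominator and, read literally, is not the quantity that the sample size was planned on

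*Protocol article*

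**What the plan says.** The Sample size section introduces eta squared as the effect size index and takes it from an ANCOVA summary table as SS factor over SS total. On the denominator it says: "SS total is the total variation, which includes the SS factor and the sum of squares for error". It then gives descriptive thresholds, beginning with "≥0.01 is regarded as a small effect", with 0.06 for medium and 0.14 for large.

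The planning effect is 0.14 on the reverse Stroop change score: "We expect to detect a large effect size". The calculation is "based on 80% power, a two-sided hypothesis test, an alpha level of 5" per cent, for "an ANCOVA model that includes a baseline reverse Stroop task score, age and sex as a covariate". The result is that "we need 32 participants in each of the combination exercise and waiting list groups with consideration of a 20% drop-out rate".

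The Analysis section fits the same kind of model to each cognitive test: "Pre-training scores in the dependent variable, sex, age categories are covariates". Eta squared is to be reported "as an index of effect size (please see the detail in Sample Size", so the reader is sent back to the definition above. Significance is judged at P<0.05. The article names no other effect index.

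**The concern.** An ANCOVA with three covariates splits the total variation into group, covariates and error. Two indices can be formed for the group term:

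- **Classical eta squared:** SS group / SS total, with the covariate sums of squares in the denominator.
- **Partial eta squared:** SS group / (SS group + SS error), with the covariate sums of squares left out.

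The formula in the article names the first. Its gloss on the total mentions only the two terms of the second. A power calculation for the adjusted group effect needs the second. If one symbol covers one quantity in planning and another in reporting, the observed value cannot be set against the planned 0.14 or against the article's thresholds.

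A second, smaller matter is that the stated question is one of benefit. An index that runs from 0 to 1 cannot show which group did better, or by how many test items.

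**Working it through.** **Inputs from the article.** Eta squared 0.14; two-sided alpha 0.05; power 80%; two groups; three covariates (baseline, age, sex); 20% drop-out; 32 per group; all randomized participants analysed.

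**Step 1: reproduce the sample size.** Treat 0.14 as partial eta squared.

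- f² = 0.14/(1 − 0.14) = 0.14/0.86 = 0.163, so f = 0.403.
- Noncentral F test with numerator df 1, error df N − 2 − 3, noncentrality f² × N.
- The smallest N with power of at least 80% is 51 (power 0.805).
- 51/0.8 = 63.75, rounded up to 64, or 32 per group. This is the stated figure.

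The Analysis section uses age categories and does not give their number. With 4 or 5 covariate degrees of freedom the answer is still 51 (power 0.805 in both cases). With all 64 analysed and three covariates, power is 0.888.

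**Step 2: try the other reading.** Suppose 0.14 is classical and the covariates take a share R² of the total, unrelated to group. Then SS error = (1 − 0.14 − R²) × SS total, and partial eta squared = 0.14/(1 − R²). R² is an assumption.

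| Covariate R² | Partial eta squared | N before drop-out |
|---|---|---|
| 0 | 0.14 | 51 |
| 0.2 | 0.14/0.8 = 0.175 | 40 |
| 0.4 | 0.14/0.6 = 0.233 | 29 |
| 0.5 | 0.14/0.5 = 0.28 | 23 |

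Once the covariates explain a material share of the variance, the stated size no longer reproduces under this reading. The planned number therefore corresponds to the partial form.

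**Step 3: what the literal formula would report for an effect exactly as planned.** By the same relation, classical = partial × (1 − R²).

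- R² = 0.1: 0.14 × 0.9 = 0.126
- R² = 0.2: 0.14 × 0.8 = 0.112
- R² = 0.4: 0.14 × 0.6 = 0.084

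All lie below 0.14 and above 0.06, so the planned large effect would carry the medium label.

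**Step 4: is that R² range reasonable?** A baseline covariate normally explains part of a change score. With equal pre and post SDs and pre-post correlation r (assumed), baseline alone explains (1 − r)²/[2(1 − r)] = (1 − r)/2 of change-score variance. That is 0.25 at r = 0.5 and 0.10 at r = 0.8, giving reported values of 0.14 × 0.75 = 0.105 and 0.14 × 0.90 = 0.126. Age and sex could only add to this.

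**Step 5: effect on the test.** The group F test uses SS group and SS error only, so the choice of denominator does not change the P value. With 64 analysed and error df 59, P<0.05 requires partial eta squared of about 0.064 (F = 59 × 0.0636/0.9364 = 4.0).

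**The case against.** **The definition is not wrong.** SS factor over SS total is ordinary classical eta squared. The word used for the total is inclusive, not exhaustive, so the covariate terms may be part of it. This stands: a reader might infer that the index is mis-defined, but the text supports only the charge of ambiguity.

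**Nothing in the design depends on it.** This also stands. A reader might infer that the trial is underpowered. Step 2 shows the reverse: if 0.14 is classical, fewer participants are needed than planned.

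**The low threshold might seem to turn noise into effects.** With no true effect, 64 analysed and three covariates, partial eta squared reaches 0.01 with probability 0.443. A reader might infer that many null outcomes would be presented as small effects. The document does not support this. The thresholds are descriptive and stand beside the planning value, results are judged at P<0.05, and the article nowhere says that non-significant results will be labelled. The 0.443 also belongs to the partial form only. With the covariates in the denominator, simulation gives about 0.43 at covariate R² = 0, falling to 0.21 at 0.6 (R² assumed).

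**Adjusted differences and intervals may be in a fuller document.** That is fair. The article condenses a protocol, and naming eta squared does not exclude other measures, so their absence is not an error. What can be said is that the one index the article commits to is unsigned and unitless. The dependent variable is a signed change score in test units, so a better measure is already within reach.

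What survives is the mismatch: the sample size matches one quantity, and the reporting formula, taken as written, yields another.

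**Conclusion.** The point holds as one of definition and reporting, of modest weight. The article leaves open whether the covariate sums of squares belong in the denominator. The sample size matches partial eta squared, while the literal reporting formula gives classical eta squared. Under that formula an effect exactly as planned would be reported as 0.126 to 0.084, below the article's own threshold for large. This rests on two assumptions: that covariates explain 10% to 40% of change-score variance, and that they are unrelated to group, as randomization gives on average. If the covariates explain nothing, the two indices coincide and the discrepancy disappears.

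The 32 per group is confirmed, and the test at P<0.05 and its error rate are untouched. The further weakness is that the named index conveys neither the direction of an effect nor its size in test items.

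**What to change.** State once, and use in both Sample size and Analysis, that eta squared means partial eta squared, SS group/(SS group + SS error), from the ANCOVA with pre-training score, age and sex. Say that the planning value of 0.14 is on that scale.

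For each score, make the covariate-adjusted mean group difference in test units, with its 95% confidence interval, the effect measure. Partial eta squared can stay beside it as a descriptive supplement.

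The cost is a few sentences of wording. The same ANCOVA already yields the adjusted difference, its interval and the two sums of squares. Sample size, data collection and the hypothesis test do not change.

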### Analysis

This study is designed to evaluate the beneficial effect of the short-term combination exercise in older people. We calculate the change score (post-training score minus pre-training score) in all cognitive function measures. We conduct an ANCOVA for the change scores in each cognitive test. The change scores are the dependent variable. Groups (combination exercise, waiting list) are the independent variable. Pre-training scores in the dependent variable, sex, age categories are covariates to adjust for background characteristics and to exclude the possibility that any pre-existing difference of measure between groups affects the result of each measure. The level of significance is set as *P* <0.05. This study reports η^*2*^ as an index of effect size (please see the detail in Sample Size). Missing data are imputed using Missing Value Analysis in the Statistical Package for the Social Sciences (SPSS). In particular, we impute missing values using maximum likelihood estimation based on the expectation-maximization algorism with the observed data in an iterative process [55]. All randomized participants are included in the analyses in line with their allocation, irrespective of how many sessions they complete (intention-to-treat principle). All analyses are performed using the SPSS (version 18 or higher; SPSS Japan Inc.).

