### Inclusion and exclusion criteria

The purpose of this intervention is to investigate the beneficial effects of combination exercise training on diverse cognitive functions in healthy older adults. Criteria include participants who report themselves as right-handed, native Japanese speakers, unconcerned about their own memory functions, not using medications known to interfere with cognitive functions (including benzodiazepines, antidepressants, and other central nervous system agents), and having no disease known to affect the central nervous system, including thyroid disease, multiple sclerosis, Parkinson disease, stroke, severe hypertension (systolic blood pressure over 180, diastolic blood pressure over 110), and diabetes. The age of participants is more than 60 years old. We elicit the above information using a semi-structured telephone interview and self-report questionnaire. We check blood pressure at the start of this intervention study.

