
### Randomization

Randomization is designed to take place after receiving the informed consent statement. A researcher (RN), who has no contact with the study participants, assigns participants to either the combination exercise group or the waiting list group by a random allocation sequence. The random allocation sequence will be generated by the Microsoft Excel 2003 program with the RAND function with no blocks and restrictions. Letters are used to inform participants of their allocation.

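### Age enters the sample-size model as age but the analysis model as unspecified age categories; one form should be named, preferably age in years

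*Protocol article*

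**What the plan says.** The Sample size section of the protocol article bases the calculation on "an ANCOVA model that includes a baseline reverse Stroop task score, age and sex as a covariate". It sets the target with "We expect to detect a large effect size (η^2^ = 0.14) of the change score" and concludes that "we need 32 participants in each of the combination exercise and waiting list groups with consideration of a 20% drop-out rate".

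The Analysis section describes the model for the change score of every cognitive test, the primary one included: "Pre-training scores in the dependent variable, sex, age categories are covariates to adjust for background characteristics". It does not say how many age categories there are or where they are cut.

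Two other sections might have supplied bands, but do not. Under Inclusion and exclusion criteria the rule is "The age of participants is more than 60 years old", with no upper limit and no strata. Under Randomization the sequence is "generated by the Microsoft Excel 2003 program with the RAND function with no blocks and restrictions", so there is no age stratification for the analysis to mirror.

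**The concern.** Read together, the two sections leave it unclear which primary model is planned. A single cut, three bands or five-year bands would all comply with the Analysis section, and a plain age term would match the Sample size section.

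Two things are at stake. The first is precision: grouping a prognostic variable discards part of what it explains. The second is that an open choice of bands permits several primary models, each with its own P value. The same ANCOVA serves all the secondary tests, so the ambiguity is not confined to the primary outcome.

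**Working it through.** **1. Reproduce the planned size.** Inputs from the Sample size section: η² = 0.14, 80% power, two-sided 5% level, three covariates, 20% drop-out.

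- f² = η²/(1 − η²) = 0.14/0.86 = 0.1628.
- Noncentrality λ = N·f²; with N = 51, λ = 51 × 0.1628 = 8.30.
- F test on 1 and N − 2 − 3 = 46 degrees of freedom: power 0.805.
- 51/0.8 = 63.75, rounded up to 64, or 32 per group. This matches the article.

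**2. Extra age terms in that calculation.** Covariates enter only by their number. With 3 to 6 covariates the required N stays at 51, and power at N = 51 goes from 0.805 to 0.804. The figure of 64 therefore does not depend on the form of age.

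**3. Information lost by grouping.** Let r be the partial correlation of age with the change score, given baseline and sex, and k the share of the variance of age that the bands retain. If the age effect is linear, the residual variance is multiplied by

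v = (1 − r²k)/(1 − r²),

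and f² becomes f²/v. The article gives neither r nor the age distribution, so both are assumed: r from 0 to 0.5, and ages either uniform on 60-80 or normal with mean 68 and SD 5 (values below 60 set to 60).

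Example: r = 0.3 and k = 0.75 give v = (1 − 0.09 × 0.75)/(1 − 0.09) = 0.9325/0.91 = 1.025.

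Power at N = 51, against 0.805 with age ungrouped:

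| Bands (assumed ages) | k | r = 0 | r = 0.2 | r = 0.3 | r = 0.5 |
|---|---|---|---|---|---|
| Cuts at 65, 70, 75 (uniform) | 0.937 | 0.805 | 0.804 | 0.802 | 0.796 |
| Tertiles (normal) | 0.819 | 0.805 | 0.802 | 0.798 | 0.782 |
| Cut at 70 (uniform) | 0.75 | 0.805 | 0.801 | 0.796 | 0.773 |
| Cut at 75 (normal) | 0.325 | 0.805 | 0.794 | 0.780 | 0.722 |

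The values r = 0.2, 0.3 and 0.5 correspond to age explaining 4%, 9% and 25% of the residual variance (r²). The last row is an unfavourable case: a single cut far from the centre of the ages, which loses about 8 points at r = 0.5.

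**4. Simulation.** Step 3 takes the groups as balanced on the bands. Simulated trials also carry the cost of chance imbalance. The settings were 51 completers, simple randomization, an effect of 0.81 residual SD (2f = 0.807) and assumed right-skewed ages 61-88.

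- *Age explains 0-4%:* single-cut and three-band schemes lose about 0-2 points against continuous age; five-year bands lose about 2.5.
- *Age explains 10%, 20%, 30%:* power is 79%, 79%, 77% with continuous age, against 75-77%, 74-76%, 72-74% with categories. That is a loss of 2-4, 3-5 and 3-5 points. A repeat of the simulation put the range at about 1-5 points.
- *No treatment effect, one fixed scheme:* type I error 4.6-6.0%, which is 5% within simulation error.
- *No treatment effect, smallest P value taken:* 7.4-8.1% over five models (continuous age and four groupings). Over eight groupings it is about 6-7% at r = 0, 8% at r = 0.3 and 9-10% at r = 0.5.

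**The case against.** The strongest reply is that this is a difference of wording. The Sample size section never says that age is continuous, so the Analysis section may only be stating the same covariate more specifically. Because the power calculation counts covariates and does not use their form, a reader who infers that the trial was powered on one model and will be analysed with another goes further than the article allows. That part of the reply stands, and so does its corollary that 64 is not put in doubt.

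A reader might also infer that the cut-points will be chosen after the data are seen. The article does not say so. Band limits are a detail that an analysis plan may fix, and that plan is not shown. The raised type I error belongs to a hypothetical search, not to anything proposed, and any pre-set bands give a valid test.

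Nor is a loss of precision certain. It requires age to predict the change score beyond baseline and sex, and nothing in the article shows how strongly it does over four weeks. If it does not, grouping loses no information on age, and the only cost is that of extra terms. If the age effect is strongly non-linear, bands need not lose precision at all.

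What the reply does not remove is the disagreement itself. The article states the covariate set twice, in two forms, and a reader cannot tell which is meant.

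**Conclusion.** The point holds as an inconsistency with a modest, conditional cost. Age is named in one section and unspecified age categories in the next, and nothing else in the article supplies bands.

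If the age effect is roughly linear, grouping cannot help. With 51 completers the cost is about 0-2 points of power (up to about 3 with five-year bands) when age explains 0-4% of the residual variance, and about 1-5 points when it explains 10-30%; a badly placed single cut could cost more. Type I error is near 5% for any scheme fixed beforehand and about 6-9% if the best of several is picked afterwards, the exact figure depending on how many schemes are tried. All these sizes rest on assumed age distributions and age effects. The sample size of 64 stands.

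**What to change.** In the Analysis section, replace age categories with age in years as a continuous covariate, and say in the Sample size section that age is in years. Both then name one model: change score on group, pre-training score, age in years and sex.

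The cost is one phrase in each section. Age has to be known for eligibility, so no new data are needed, and the sample size does not change. The small downside is that a single continuous term assumes a linear age effect. If categories are preferred for that reason, state their number and cut-points in both sections before outcome data are seen; that equally closes the choice between models. The article reports recruitment as still under way, so either repair could be recorded in advance.
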